#### Intention-to-treat (ITT)

Outcome will be analyzed under the basis of ITT. First, the principles of ITT will be applied to test the effects of attrition, which means that all participants who have been randomized will be included in the analysis. Missing endpoints will be imputed by using the Expectation-Maximization (EM) algorithm. To gauge the robustness of the outcomes, this analysis will be repeated while using Multiple-Imputation approach. Second, propensity Score analysis will also be used. By using logistic model (1 for adherence and 0 for attrition) to predict the probability of be in adherence. And then use the predicted variable to replace the attrition dummy variable.

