### Setting

Subjects recruitment will be performed in Changsha, provincial capital of Hunan province, China. The city has over 6 million people, including 15 thousand MSM. Implementation of this study will be cooperated with Chagnsha CDC. It is the authoritative HIV testing institution, and has the right to verify one’s HIV-positive status. In addition, the center takes charge of two non-governmental organizations (NGO) which exclusively providing HIV testing and counseling services for MSM. These organizations have built good relationship with MSM.

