## Participants

### Inclusion and exclusion criteria

Participant inclusion criteria: (1) male aged 16 years or older, (2) has experience of same-sex anal intercourse during the last 12 months, (3) HIV negative, (4) own at least one smartphone, and (5) willing to report individual HIV/STDs testing results to the researcher. Participant exclusion criteria:(1) has only one sex partner who is also HIV negative, and their relationship has last for more than 2 years, (2) unable to participant the program because of cognitive or psychiatric disorders, or (3) has already attended another intervention program.

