#### Sample size and calculation

The intervention arm and control arm are of equal size and two-tailed hypothesis testing is assumed. Sample size is calculated by using the specific sample size function module PASS on the statistical analysis software NCSS [42]. By setting the α = 0.05, 1-β = 0.9, effect size as 0.25 [43], the sample size of each group is 336. With an estimated 20% loss to follow-up, 400 subjects are necessary for each group.

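### The planned checks on missing HIV endpoints all assume that dropout is unrelated to unobserved HIV status, so they cannot show whether infection-related dropout changes the result

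*Protocol article*

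**What the plan says.** The protocol article (Intention-to-treat section) keeps everyone in the analysis: "all participants who have been randomized will be included in the analysis". For men without an outcome, "Missing endpoints will be imputed by using the Expectation-Maximization (EM) algorithm". Robustness is to be judged because "this analysis will be repeated while using Multiple-Imputation approach". A second step fits a logistic model for adherence versus attrition and uses the predicted probability in place of the attrition indicator.

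Other sections that bear on this:

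- Sample size: "With an estimated 20% loss to follow-up, 400 subjects are necessary for each group".
- Outcome measures: HIV/STD infection rates and the relative risk of infection are primary. Adherence to regular HIV testing is secondary.
- Inclusion criteria: participants must be "willing to report individual HIV/STDs testing results to the researcher".
- Data collection: the follow-up questionnaire reaches the intervention arm inside the app and the control arm by Wechat.
- Participant follow-up: a man found infected is withdrawn, so his HIV endpoint is already known.
- Setting: of the partner CDC the article says "It is the authoritative HIV testing institution, and has the right to verify" a man's positive status. The CDC also takes charge of two NGOs that test MSM.

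The article does not say whether CDC results will be sought for men who are lost.

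**The concern.** EM, multiple imputation and a propensity model of attrition differ in how they handle variance and weighting. In ordinary use all three learn about the missing men from the observed data alone. If two men with the same recorded history differ in their chance of staying because one has become infected, none of the three can detect it. Running the second and third therefore does not test the assumption behind the first.

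That assumption is open to doubt here. The outcome depends on a man's willingness to report his test results, and one who tests positive, or expects to, has a reason to stop. The follow-up channels also differ by arm, so the amount of loss and the reasons for it may differ too. A fifth of each arm is expected to be lost on an outcome with probably few events, so a modest number of unseen infections in one arm could create or hide an effect.

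**Working it through.** **Inputs from the article:** 400 per arm, 20% loss, 336 per arm before loss, two-sided test, and "By setting the α = 0.05, 1-β = 0.9, effect size as 0.25" (the type of effect size is not stated).

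**Assumed, because the article gives no incidence:** an 18-month HIV risk of 5% or 10% among completers, dropout risks of 5% to 20%, and the look-up sensitivities in step 4.

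**1. The plan's own figure.** Read as a standardised difference, n = 2 × ((1.95996 + 1.28155) / 0.25)² = 336.24 per arm, which reproduces 336. The 400 is close to 336 × 1.2 = 403.2. Dividing instead gives 336 / 0.8 = 420, and 400 covers a loss of only 1 − 336/400 = 16%. That is a separate matter. What counts here is that 20% of 400 leaves 320 observed and 80 missing per arm, or 160 of 800.

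**2. What the planned imputation would show.** Take equal completer risk in both arms, intervention dropouts at the completer risk, and recorded covariates that do not explain the excess. Infections per arm = 320 × completer risk + 80 × dropout risk. Both arms have 400 men, so the relative risk is the ratio of counts.

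| Completer risk | True control-dropout risk | True, intervention vs control | True RR | After imputation | RR shown |
|---|---|---|---|---|---|
| 5% | 5% | 16+4=20 vs 16+4=20 | 1.00 | 20 vs 20 | 1.00 |
| 5% | 10% | 20 vs 16+8=24 | 0.83 | 20 vs 20 | 1.00 |
| 5% | 15% | 20 vs 16+12=28 | 0.71 | 20 vs 20 | 1.00 |
| 10% | 15% | 32+8=40 vs 32+12=44 | 0.91 | 40 vs 40 | 1.00 |
| 10% | 20% | 40 vs 32+16=48 | 0.83 | 40 vs 40 | 1.00 |

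With the arms reversed in the third row, a true 28/20 = 1.40 also appears as 1.00. If both arms' dropouts have 15%, the truth is 28 vs 28 and the relative risk of 1.00 is right. What matters is a difference between arms.

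**3. What an adequate check would vary.** Let δ be the ratio of dropout risk to completer risk, set separately per arm. At 5%, letting each δ run from 1 to 3 moves the relative risk from 20/28 = 0.71 (δ = 3 in control only) to 28/20 = 1.40 (δ = 3 in intervention only). The planned analyses in effect stay at δ = 1 in both arms.

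**4. What a CDC check can and cannot add.** A record of confirmed positives identifies positives only. Let p be the risk among the 80 lost men and s the share of their infections that the record finds. Then 80ps are found, 80(1 − ps) are unmatched, and the residual risk among the unmatched is p(1 − s)/(1 − ps).

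- p = 5%, s = 75%: 3 found and 77 unmatched, with residual risk 0.0125/0.9625 = 1.3%, or 1 infection. The total is 4, which is correct. Imputing the 77 at 5% gives 3 + 3.85 = 6.85, too many. Counting them as negative gives 3, too few.
- p = 10%, s = 75%: 6 found and 74 unmatched, with residual risk 0.025/0.925 = 2.7%, or 2 infections. The total is 8. Imputing the 74 at 5% gives 6 + 3.7 = 9.7.
- For a fixed number found, the implied total is found/s. Three found means 4 infections at s = 75%, 6 at 50% and 12 at 25%, so s needs a stated range.
- Suppose s is 30% in control and 60% in intervention, there is no true effect, and unmatched men count as negative. The relative risk shown is (0.8 + 0.2 × 0.6)/(0.8 + 0.2 × 0.3) = 0.92/0.86 = 1.07.

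**The case against.** Four points can be made on the other side.

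**Imputation under missing-at-random is a normal primary choice.** With good predictors from baseline and earlier visits it may be close enough. This stands, and the point is not against EM or multiple imputation as the main analysis. It concerns a stated robustness check that leaves the doubtful assumption untouched.

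**The article is condensed.** Tracing of lost men, retrieval of CDC results and consent wording may sit in the full protocol. This also stands, and silence on them is not counted as a fault. The robustness check itself is stated, and it is the part criticised. The CDC check is offered as an addition.

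**The illustrated risks are assumed, and the excess is placed in one arm.** True. The missed 4 or 8 infections at 5% completer risk are 4/24 = 17% or 8/28 = 29% of that arm's true total, and an equal excess in both arms would leave the relative risk unchanged in the example. The figures show what the planned checks could miss, not what will happen.

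**A look-up can add bias.** Step 4 confirms this for unmatched men imputed at the completer rate or counted as negative, and for detection that differs by arm, which is plausible because the app promotes testing. It is a reason to specify the analysis of unmatched men.

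A reader might infer that most of the missing HIV endpoints could simply be looked up. The article does not support that. It gives the CDC authority to verify positives, but does not describe a searchable record, access for the trial or coverage of most lost men. Untested men and those confirmed elsewhere would not be found, and nothing shows that STD results are held there. Nor is imputation the only stated handling, since the propensity model is also planned. The text imputes missing endpoints; it does not say that a man who stops using the app is treated as missing.

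**Conclusion.** The point holds as a weakness in a stated method. The planned checks share one assumption, so they cannot tell whether dropout related to infection alters the primary comparison. At the planned loss, up to 160 of 800 men would have an imputed endpoint. With 5% completer risk and dropout risks between 5% and 15% that may differ by arm, a true relative risk anywhere from 0.71 to 1.40 could be shown as 1.00. At 10% completer risk, control-dropout risks of 15% to 20% put the truth at 0.91 to 0.83 against a shown 1.00. These sizes rest on assumed risks, on the excess falling in one arm, and on covariates that do not explain it.

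Consented CDC-confirmed results could settle part of the missing HIV endpoints, not most, and the article shows nothing comparable for STDs. They are supplementary data and do not replace the sensitivity analysis. The change is worth making, but the planned imputation is not invalid as a primary analysis.

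**What to change.** **In the Intention-to-treat section:**

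1. Add a delta-adjusted or tipping-point multiple imputation in which HIV risk among dropouts varies separately by arm over a range fixed in advance. Report where, if anywhere, the conclusion changes.
2. Report the number of imputed HIV and STD endpoints per arm.

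This needs no new data and only modest programming.

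**In addition, in the consent described under Recruitment:** ask at enrolment for permission for the partner CDC to check confirmed-positive results at month 18 for men lost to follow-up, under the same procedure in both arms. In the analysis:

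3. Use a confirmed positive result where one is found.
4. Do not count unmatched men as negative or impute them at the full completer rate. Their imputed risk must allow for the search having found nothing, for example p(1 − s)/(1 − ps), over a stated range of look-up sensitivity s that may differ by arm.

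**Cost and downsides:** a consent item and one record check, if the CDC can provide it. Some men may decline. Linkage needs a protected key, because the article describes anonymous data entry and promises confidentiality. Untested men and those confirmed elsewhere are missed, detection may differ by arm because the app promotes testing, and missing STD endpoints are not helped.

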#### Analysis of intervention mechanism

Correlation analyses between each aspect of participants’ app use behaviors (e.g. app use frequency and time durance, information scanned, interaction frequency) and effectiveness of the intervention will be performed. A causal path model will be built according to correlation analyses results and related theories. And a path analysis will be subsequently conducted so as to calculate the residual path coefficient and determination coefficient, define causal relationships between different variables, and thus explore intervention mechanism of the app-based intervention.

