## Procedures

### Phase 1: Development of the app

First, on the basis of our previous studies and references reviewing, preliminary functional modules of the app were presented in Table 1 below. Next step of this study is to search and evaluate currently exist domestic HIV/STDs prevention and treatment related apps on Apple.

**Table 1 Tab1:** Function modules of HIV prevention app for MSM

Name	Function description
Behavioral assessment	Assessment about user’s unprotected sex behaviors and condom use rate
Behavior change plans	Setting personal goals and plans of health behavior change, and individualized reward/punishment plans
Counseling	Buttons for enter into phone, message, Wechat and email counseling areas
Health education	Knowledge about HIV diagnosis, prevention and treatment, skills of condom using, etc
Personal health records	Uploading HIV/STDs testing results, building personal health records and health promotion plans
Information push	Delivering latest news HIV prevention, treatment and related policies, and reminders of personal behavior, encouragement and advice
Experts encouragements	Videos from professionals and celebrities to encourage user’s adherence to behavior change efforts
Institutions introduction	Providing information about addresses, connection methods, providers and services offered of CDC, hospitals, NGOs nearby
Feedback platform	Building a communication platform where users can give feedback of using the app
Setting	Settings of time period of receiving information, passports of log in the app, latest versions, etc

Store and Android Market since the two markets occupy 90.61% of the current mobile application markets [41]. We use the words “HIV/AIDS/human immunodeficiency virus/STD/ sexually transmitted disease/sexual health/sexual behavior/positive sex/condom” respectively to search for related apps, each eligible app will be downloaded and its features, including names, download numbers, target population, main function modules will be listed and analyzed.

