### Phase 2: Effectiveness evaluation of the app-based intervention

#### Intervention description

Participants in the intervention arm will receive app-based intervention. Each of them will be required to download the app and register as a user consequently, their accounts information, e.g. account name, email address used for registration will be collected. Four disciplines will be taken into account during the intervention period: (1) Interaction: at least once interaction will be required between the user and the app per week (e.g., sexual risk behavior report). (2) Non-stigmatization: a supportive atmosphere including social, behavioral, and psychological support will be built, and all contents will be presented without sense of discrimination. (3) Motivation encouragement: design and development of the app, information offered by the app will be in line with users’ needs, willingness and preferences so as to inspire their using motivation and maintain their adherence of the intervention. And two methods, health behavior goals setting according to the user’s sexual risk behavior, and exchange for free condoms with points earned by using the app regularly will be involved as incentive approaches to increase individual’s motivation of behavior change. (4) User-experience-centric: the app-based intervention will be user-oriented and we lay emphasis on user experience from aspects of interface and function modules as well.

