#### Data collection

Baseline data of all the subjects will be collected at the enrollment procedure. The measures including demographic information (*age, marital status, current occupation, educational level, income and sexual orientation*), sexual behaviors (*number of male and female sex partners, frequency of sex, sex role, commercial sex behaviors, sex with fixed and casual sexual partners*), and health-related behaviors (*consistent condom use with multi-type of sex partners, regular HIV testing, drug use experience and sexual transmitted diseases infection history*).

For the rest three times of data collection, sexual behaviors, health-related behaviors, and app user experience (*user experience, feedback and suggestions*) during the last 6 months will be involved in an electronic questionnaire. One version will be made into the app and be delivered every 6 months to intervention arm participants. Another without app user experience items will be delivered by Wechat to the ones in control arm.

Data of cost of the intervention and participants’ app use behaviors will also be collected. Direct cost involves cost of development, operation and maintenance of this app and worker cost, indirect cost consists of participants’ expenses due to their joining in the study such as time spending, cell phone internet data and traffic cost. App use behaviors will be collected through the management system which involves participants’ use frequency and time durance, information scanned, interaction times and frequency.

We use the electronic questionnaire to make sure that all of the items will be presented in a logical order and necessary answers missing will not be allowed. The participant will be offered a non-cash financial compensation as phone bills worth 20 RMB for compensation every time he complete the data collection.

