#### Outcome measures

Outcomes will be compared between intervention and control arms, and between different time points of each arm. The primary outcomes include HIV/STDs infection rates, relative risk of HIV/STDs infection, secondary outcomes include condom use rates, adherence to regularly HIV testing. The incremental cost is defined as per HIV infection case decreased according to the app-based intervention, cost of every 1% decrease of HIV/STDs infection, or every 10% increase of consistent condom use and adherence to regularly HIV testing. Another outcome is the app-based intervention mechanism (detailed below).

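### Uploading an HIV test result can itself count as app use, so part of any link between app use and testing in the mechanism analysis may run from outcome to exposure

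*Protocol article*

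**What the plan says.** Four parts of the Protocol article bear on this.

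- **Exposure.** Analysis of intervention mechanism lists, as examples, "app use frequency and time durance, information scanned, interaction frequency". Data collection takes these from the app's management system, as "use frequency and time durance, information scanned, interaction times and frequency".
- **Outcome.** Each aspect of use is correlated with the effectiveness of the intervention. The Abstract and Analysis of intervention outcomes both count regular HIV testing under effectiveness, and Outcome measures states "secondary outcomes include condom use rates, adherence to regularly HIV testing".
- **What men do inside the app.** Table 1 (Phase 1: Development of the app) gives the personal health records module as "Uploading HIV/STDs testing results, building personal health records and health promotion plans". Intervention description says "at least once interaction will be required between the user and the app per week (e.g., sexual risk behavior report". Data collection says of the follow-up questionnaire: "One version will be made into the app and be delivered every 6 months to intervention arm participants".
- **Use made of the correlations.** "A causal path model will be built according to correlation analyses results and related theories", and the path analysis is then meant to define the causal relationships between variables.

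The article does not distinguish events that report an outcome from events that deliver the intervention.

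**The concern.** For HIV testing, the exposure may contain the outcome. A test gives a result, the result is uploaded, and the upload is an interaction in the log. The count then rises because the man tested, not the other way round. It can raise use frequency and duration too, since an upload needs a session and takes time.

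The analysis takes place within the app arm, so randomisation gives no protection. Mechanism is a stated objective of the study. A correlation produced partly by counting would enter the path model as evidence that using the app makes men test more.

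**Working it through.** The protocol gives no figure for app use or for the size of this correlation, so there is none to reproduce. The check asks how large a correlation the counting alone can produce when the app has no effect.

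**Inputs from the protocol**
- Men in the app arm with follow-up: 400 × (1 − 0.20) = 320 (Sample size and calculation).
- Required use: one interaction per week, i.e. about 26 per 6 months or 78 over 18 months (Intervention description).

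**Assumptions (none given in the protocol):** mean and spread of other app use, the probability of testing, and the number of logged events per test.

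**Check 1: one 6-month window.** Half the men test, independently of use. Other use is a gamma-Poisson count with mean m and variance m + d·m². A tester gains k logged interactions. The Spearman correlation of use with testing is tested at 5%.

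With k = 1, and d = 0.3 or d = 0.8:

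| Mean other use per 6 months | Trials with a significant correlation |
|---|---|
| 26 | about 8 to 10% |
| 10 | about 30% |
| 5 | about 74 to 80% |

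The nominal rate is 5%. With k = 2 or 3 the rates are 26% and 52% at a mean of 26 (d = 0.3), and 72% and 98% at a mean of 10 (d = 0.8). At a mean of 5 they are close to 100%.

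**Check 2: 18 months, up to six tests.** The number of tests T is binomial(6, 0.5), with variance 6 × 0.5 × 0.5 = 1.5. Logged use is U = G + kT + 3, where G is other use, independent of T, and the 3 are the follow-up questionnaires. Then

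r(U, T) = k√1.5 / √(Var G + 1.5k²).

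With k = 1:
- G Poisson, mean 5: 1.225/√(5 + 1.5) = 0.48.
- G negative binomial with shape 1, mean 5 (variance 5 + 25 = 30): 1.225/√31.5 = 0.22.
- G Poisson, mean 78: 1.225/√79.5 = 0.14.
- G negative binomial with shape 1, mean 78 (variance 78 + 6084 = 6162): 1.225/√6163.5 = 0.02.

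Simulation with 320 men gave the same values. Results were significant in 97 to 100% of runs at a mean of 5 and in 6 to 69% at a mean of 78.

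**Check 3: sexual behaviour.** In the same simulation, logged use was correlated with a condom-use indicator unrelated to app use. The correlation was 0.00 and 4 to 6% of runs were significant, which is the nominal rate. The constant 3 drops out of the formula in Check 2, so the questionnaires add nothing among men who complete all of them.

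**The case against.** **The behaviour outcomes.** A reader might infer that weekly risk reports and the in-app questionnaire also tie app use to sexual behaviour. The text does not support this. Weekly interaction is required of every user, with the risk report as an example, so it is not triggered by having sex. A report counts once whatever it says. Check 3 shows no link by counting alone. One would need something more, such as a shared engagement trait or reporting that varies with risk. This objection stands and confines the point to HIV testing. The amount of information viewed is likewise not a reporting act.

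**The window.** A reader might infer that use and outcome cover the same 6 months. The 6-month recall is stated only for the questionnaire; no window is given for the logs.

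**Detail left elsewhere.** The coding of log events may be set out in a fuller document, and Table 1 calls its modules preliminary. Exclusion of uploads is unstated, not ruled out. That limits the claim to what may happen. It does not remove it, because the article fixes the exposure as logged interactions, makes uploading an app function, and assigns the correlations a causal role.

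**Size.** If men meet the weekly requirement and one test makes one event, the inflation in Check 1 is small. The large figures need use well below that requirement or several events per test. This is fair. Still, the Background itself warns that the app has no value if men do not use it, so low use cannot be dismissed.

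**Importance.** Mechanism is neither a primary nor a secondary outcome, and the stated aim is partly to explore it. This too is fair, and it is why the point is not graded higher.

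**Conclusion.** The point holds for HIV testing only. As described, testing can raise logged use frequency, duration and interaction counts, so part of any association between app use and testing may run from outcome to exposure.

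The direction of this artefact is positive. Its size is unknown, because it depends on what share of logged use consists of uploads: near the nominal error rate when use is frequent and variable, and severe when use is sparse. All use rates, spreads and events per test above are assumptions, and the effect on duration was not quantified.

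A reader might also infer that the trial's effectiveness results are compromised. They are not: the comparisons between randomised arms do not use app-use logs. What is at risk is the causal reading of one path in the mechanism analysis. This should be corrected, and it is cheap to correct while the app is still being built.

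**What to change.** In Data collection and Analysis of intervention mechanism:

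1. Tag result-upload events and in-app outcome-questionnaire sessions in the management system. Leave both out of app-use counts and durations when use is related to HIV testing. Omitting uploads removes the mechanical part by construction; omitting questionnaires keeps measurement apart from exposure.
2. Keep risk reports and the other modules in the exposure, since they are intervention content, and report risk reports as a separate component. Removing them from every exposure would delete part of what the analysis sets out to study.
3. Relate use in one 6-month window to testing in the next (months 0–6 to 6–12, and 6–12 to 12–18). Adjust for earlier testing only as a sensitivity analysis: if early use raises early testing, that adjustment may block part of the effect.
4. Describe the path analysis as exploratory, not as defining causal relationships.

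The cost is event tagging, best built in during app development because event types that were not logged may not be recoverable, plus some rewording. The lagged analysis does not use the 6-month outcome or the app use in months 12–18.

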**Discussion:**

This will be the first study of its kind in China to develop an app and implement app-based HIV prevention intervention among MSM. It is of great potential to determine whether app-based intervention is a cost-effective way to decrease HIV infection among MSM and explore intervention mechanism with an accurate method.

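### The mechanism analysis can describe associations with self-selected app use, but it cannot define causal relationships as the protocol says it will

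*Protocol article*

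**What the plan says.** The section Analysis of intervention mechanism describes three steps.

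1. "Correlation analyses between each aspect of participants’ app use behaviors" and the effectiveness of the intervention are run first.
2. Then "A causal path model will be built according to correlation analyses results and related theories". No theory is named.
3. A path analysis follows, which is to "define causal relationships between different variables", "and thus explore intervention mechanism of the app-based intervention".

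On the exposure, Data collection states: "App use behaviors will be collected through the management system which involves participants’ use frequency and time durance, information scanned, interaction times and frequency". Intervention description makes the app the treatment of one arm: "Participants in the intervention arm will receive app-based intervention". It sets a minimum of one interaction a week and encourages further use through an incentive, the "exchange for free condoms with points earned by using the app regularly".

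Mechanism is among the aims in the Background and is listed as a further outcome under Outcome measures. The abstract's Discussion says that the trial can "explore intervention mechanism with an accurate method". The main Discussion counts accuracy in illustrating the mechanism as a strength. Its paragraph on limitations deals with the lack of masking and does not mention that the amount of use is chosen by the participant.

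**The concern.** Randomisation makes the two arms comparable. It does not make heavy and light users within the app arm comparable. Men who are already motivated to protect themselves may use the app more and also use condoms and test more, whatever the app does. The protocol itself links use to motivation, since it relies on inspiring motivation to keep men using the app.

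Direction is also open. A report of sexual risk behaviour is given as an example of an app interaction, so behaviour can feed into the use measure. Men who become infected are withdrawn, so if use is totalled over follow-up, infection could shorten it. A path model fitted to such correlations takes the direction of its arrows as an input and does not discover it.

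Finally, the correlations that help to choose the paths come from the same data in which the paths are then estimated. Paths kept for that reason tend to be overestimated.

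At stake is a stated aim of the study. A reader could be told that more app use causes safer behaviour on evidence that cannot show it.

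**Working it through.** **The plan's own figure.** The mechanism section states no number, so there is none to reproduce. The calculations below only illustrate how large the problem could be.

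**Inputs from the protocol**
- Men per arm 400, loss 20% (Sample size and calculation): 400 × 0.80 = 320 men in the app arm.
- Two-sided α = 0.05 (same section).
- Four app-use aspects, given as examples in the mechanism section: frequency, duration, information scanned, interaction frequency.
- Four outcome groups under Analysis of intervention outcomes: HIV/STD infection, consistent condom use, regular testing, sexual risk behaviour.

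**Inputs assumed**
- App use has no effect on the outcome.
- An unmeasured trait, such as motivation, has correlation *a* with both use and outcome. The protocol gives no value, so *a* runs from 0.2 to 0.5.
- Outcomes are continuous, a simplification relaxed in step 2.

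**Step 1: confounding.** The trait induces a correlation ρ = a² between use and outcome. By Fisher's z, the chance of p < 0.05 is about Φ(√(n−3)·atanh ρ − 1.96), plus a small opposite tail, with √317 = 17.80. For a = 0.4: ρ = 0.16, atanh ρ = 0.1614, 17.80 × 0.1614 = 2.87, Φ(2.87 − 1.96) = Φ(0.91) = 82%.

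| a | ρ = a² | False path significant, formula, n = 320 | Simulation, n = 320 | Simulation, n = 400 |
|---|---|---|---|---|
| 0.2 | 0.04 | 11% | 10.9% | 13.0% |
| 0.3 | 0.09 | 36% | 37.0% | 43.4% |
| 0.4 | 0.16 | 82% | 82.3% | 88.9% |
| 0.5 | 0.25 | 99.5% | 99.4% | 99.9% |

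The simulation used 4,000 runs per setting. At a = 0 it gave about 5%, as it should.

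**Step 2: binary outcomes.** The main outcomes are compared as rates. Dichotomising a latent normal outcome at prevalence p multiplies ρ by φ(z_p)/√(p(1−p)). At a = 0.4 and n = 320:
- p = 50%: factor 0.399/0.500 = 0.798, ρ = 0.128, significant in about 63%.
- p = 5% (assumed): factor 0.103/0.218 = 0.473, ρ = 0.076, significant in about 27%.

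**Step 3: screening.** With no confounding, 4 aspects × 4 outcomes = 16 correlations at one time point. If they are independent, P(at least one p < 0.05) = 1 − 0.95^16 = 56%, with 16 × 0.05 = 0.8 expected.

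**Step 4: selection in the same data.** Among null correlations at n = 320 that pass p < 0.05, the mean |r| is about 2φ(1.96)/0.05 ÷ √320 = 2.34/17.89 = 0.13, although the true value is zero.

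**The case against.** Several points on the other side are fair.

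- **Theory is also an input.** A reader might infer that correlations alone choose the paths. The protocol does not say that: related theories contribute too. This stands, but no theory is named in the article, and the correlation results remain an explicit input to the model.
- **The purpose is exploratory.** The Background, the abstract and the mechanism section all speak of exploring. That limits the stakes, yet the same sentence in the mechanism section promises to define causal relationships.
- **Missing detail is not an error here.** Covariates, time ordering and a path diagram may stand in a fuller document, and the article excludes none of them. The point therefore rests on the stated causal claim and the stated use of correlations to build the model. Adjustment elsewhere would not remove either.
- **Use is not wholly free.** A weekly interaction is required. Only use beyond that, and compliance with it, is self-selected.
- **The percentages are assumption-driven.** They depend on a trait correlation that the documents do not give, and at 0.2 the rate is only 11%. The screening figure depends on how correlations are counted. Counting three follow-up visits as well gives 48 and 1 − 0.95^48 = 91%, but the article does not say that each visit is screened, and the measures overlap, so independence is implausible.
- **Effectiveness within one arm.** A reader might object that the effect of the intervention cannot be observed in a single man. In a correlation analysis the word can reasonably mean his outcome or his change from baseline, so this is loose wording and not an analytic fault.

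**Conclusion.** The point holds in a limited form. The analysis as described relates a non-randomised, one-arm exposure to outcomes, lets correlations in those data help to shape the model, and then attaches causal status to the result. It can support statements of association only.

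The size is not a property of this trial. With no true effect, false paths would be significant in about 11% to 99% of trials as the assumed trait correlation goes from 0.2 to 0.5, with continuous outcomes and 320 men. The rate is lower for binary outcomes.

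It would go too far to say that a false mechanism will be reported. The plan permits that, and the text shown states no safeguard, but whether it happens depends on confounding and chance that the documents do not quantify. The randomised comparison, the sample size and the primary outcomes are untouched. The point deserves correction because mechanism is a stated aim and correction is cheap.

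**What to change.** - Specify the path diagram from named theory before follow-up data are seen, and do not select paths by correlation in the same data.
- Relate app use in one 6-month interval to outcomes in the next, provided the logs can be divided by interval.
- Adjust for the baseline sexual and health-related behaviours and demographics already collected.
- Replace "define causal relationships between different variables" with wording about describing associations. State that self-selected use and unmeasured motivation limit interpretation. Motivation is not among the listed baseline measures, so adjustment can only be partial.
- If a mediation analysis with randomised arm as exposure is added, using mediators measured in both arms such as condom use and testing, label it exploratory too. Randomising the arm does not remove confounding between mediator and outcome.

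The cost is a weaker claim, revised wording and a little more modelling. No new data are needed, and no figure in the protocol changes.
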